### Randomization

Participants will be randomly assigned to the intervention or control group using a computer-generated list. As age is the most significant risk factor for cognitive decline, and our study has a relatively small sample size, we will do a stratified randomization by age (45‐60 and 61‐75 y) to avoid significant baseline differences pertaining to age in the 2 groups. The sequence will be created using Stata 17 by an independent statistician. Unique IDs starting with “BRY2001-BRY2038” for younger and “BRE3001-BRE3038” for older participants will be assigned prior to allocation to ensure a systematic and unbiased process. To maintain a 1:1 allocation ratio and minimize selection bias, a block size of 4 will be applied within each age stratum. This approach ensures that participants in both age groups are evenly distributed between the intervention and placebo arms. To prevent selection bias, the randomization list will be kept strictly confidential and accessible only to the independent statistician, who will not be involved in recruitment or data collection.

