### Outcomes

The primary outcome will be change in the composite *z* score of memory between the 2 groups at 12 weeks. The memory domain will include both verbal (Verbal Learning Test: learning over trials, delayed recall, delayed recognition) and visuospatial memory (Test des Neuf Images du 93-Spatial Recall). The secondary outcomes will include alterations in metabolites, pathways, and molecular networks, and frequency of SAEs after 12 weeks of treatment with *B. monnieri*; change in *z* scores for other cognitive domains (attention, executive functioning, and information processing) at 12 and 24 weeks (including *z* score for the memory domain at 24 wk); proportion of participants in both groups who demonstrate clinically meaningful cognitive improvement, defined as either ≥5 point improvement on the ACE-III [43], or ≥0.5 SD improvement in the composite *z* score of memory domain in the *Bacopa* versus placebo group at 12 and 24 weeks. Adherence will be monitored through self-reported medication logbooks and weekly telephonic follow-ups.

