### Statistical Methods

#### Sample Size Estimation

There are no previous studies investigating the effects of *B. monnieri* versus placebo in patients with aMCI, looking at changes in composite memory *z* scores as the primary outcome. By considering a clinically relevant effect size as a SD change of 0.5, a 2-sided α at 5%, and 80% power, a sample size of 128 (64 in each group) was calculated. With a 20% dropout rate, the final sample size reached 160 (80 in each group), which did not seem feasible for the selected patient population in the specified duration. Therefore, a sample size of 60 (30 in each group) is determined for this exploratory study based on feasibility. The sample size was further adjusted for a dropout rate of 20% and 76 participants (38 in each group) will be recruited for this study.

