#### Planned Analyses

As mentioned previously, data will be entered into REDCap, a secure web-based application for managing databases. A data monitoring committee is not needed for this trial, as it is a short-duration study and the known risks of the intervention drug are minimal. No interim analysis is planned. Data will be analyzed using Stata version 17.0 (StataCorp LLC, College Station, TX, USA) and presented data as number (%), mean (SD), or median (IQR), as appropriate. Pearson chi-square test or Fisher exact test will be used (as appropriate) for qualitative variables. For quantitative variables, normality will be assessed using the Shapiro-Wilk test. The Student *t* test for independent samples will be used to compare differences in means for normally distributed quantitative variables. The Mann-Whitney *U* test will be used for quantitative variables with a distribution other than normal. All tests will be 2-tailed, and a *P* value <.05 will be considered statistically significant. Raw scores of each cognitive test will be converted to a *z* score (*z* score=[individual participant raw score – group mean]/group SD) for each participant. The group mean and SD will be derived by pooling the baseline scores of all participants. For all the tests, a higher *z* score will indicate better performance, except for the trail making tests A and B. The signs of these two tests will be inverted for a uniform interpretation. Both intention-to-treat and per protocol analysis will be done. Generalized linear mixed models with a between-subject factor of group (treatment vs placebo) and within-subject factor of time (baseline, mid-point, end point) will be conducted to assess differences in continuous primary and secondary outcome measures. Planned simple contrasts will be conducted to assess all time points (baseline vs. 12 wk, 12 wk vs. 24 wk, and baseline vs 24 wk). To handle any missing data, analysis of last observation carried forward will be undertaken within the intention-to-treat analysis model. Comprehensive statistical and functional analysis pertaining to the metabolomics will be performed using MetaboAnalyst version 6.0. The investigation based on observed peak values will encompass principal component analysis, partial least squares discriminant analysis, ANOVA, and molecular pathway identification. Heat maps will be developed with samples arranged in columns and features in rows, presented in a gradient from cold to hot. Pathway analysis will be conducted utilizing the integrated features of MetaboAnalyst 6.0, which includes the Kyoto Encyclopedia of Genes and Genomes and the Human Metabolome Database.

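### The primary mixed model treats baseline memory as an outcome level, so the week-12 arm contrast is a change-score difference: valid, but less precise than a baseline-adjusted contrast in a trial cut to 47% of its calculated size.

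*Protocol article*

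**What the plan says.** Under Planned Analyses, continuous primary and secondary outcomes go to generalized linear mixed models with a "between-subject factor of group (treatment vs placebo) and within-subject factor of time (baseline, mid-point, end point". The planned contrasts compare baseline with week 12, week 12 with week 24, and baseline with week 24. No covariate is named. The Outcomes section defines the primary endpoint in the same spirit: "The primary outcome will be change in the composite" memory z score, compared between arms at 12 weeks.

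The Randomization section says "we will do a stratified randomization by age" (45-60 and 61-75 years), and gives as reasons the importance of age as a risk factor and the small sample. The planned analyses in the article do not mention the age stratum.

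On size, the Sample Size Estimation section starts from this premise: "By considering a clinically relevant effect size as a SD change of 0.5". With "a 2-sided α at 5%, and 80% power, a sample size of 128 (64 in each group) was calculated". It goes on: "With a 20% dropout rate, the final sample size reached 160 (80 in each group"). This was judged not feasible, so "a sample size of 60 (30 in each group) is determined for this exploratory study based on feasibility", and after a dropout allowance "76 participants (38 in each group) will be recruited for this study". The limitations paragraph concedes that power is insufficient to evaluate efficacy.

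**The concern.** When baseline is a level of time and the arms have free means at baseline, the arm effect at week 12 is the difference between arms in mean change. A change score subtracts the whole baseline value, whereas the most precise adjustment subtracts only the part that predicts the week-12 score. Whenever r is below 1, the change score therefore carries extra noise. In a given trial, a chance imbalance in baseline memory also feeds into the estimate through regression to the mean.

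At stake is precision that costs no data. It matters more here than usual because the sample was set by feasibility at less than half the calculated size, and the protocol itself worries about chance imbalance in small arms. It guards against that imbalance for age by design, but not for baseline memory, which is likely to be the stronger predictor of week-12 memory.

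**Working it through.** **1. The plan's own figures reproduce.** For 0.5 SD, two-sided 5% and 80% power, the normal approximation gives n = 2(1.96 + 0.84)²/0.5² ≈ 63 per arm. The t-test solution is 63.8, so 64 per arm, or 128. With 20% dropout, 64/0.8 = 80 per arm (160), and 30/0.8 = 37.5, so 38 per arm (76). The cut is 60/128 = 46.9%, or 76/160 = 47.5%.

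**2. Variance of the two contrasts.** Take equal variances at baseline and week 12, in units of the score variance, with complete data:

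- change score: 2(1 − r)
- baseline-adjusted: 1 − r² = (1 − r)(1 + r)
- ratio, adjusted to change: (1 + r)/2, a saving of (1 − r)/2

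The documents do not give r, so it is assumed over a range. The equivalent N is 60 divided by the ratio.

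| Assumed r | Ratio | Saving | 60 adjusted participants are worth |
|---|---|---|---|
| 0.3 | 0.65 | 35% | 92 |
| 0.5 | 0.75 | 25% | 80 |
| 0.7 | 0.85 | 15% | 71 |
| 0.8 | 0.90 | 10% | 67 |
| 0.9 | 0.95 | 5% | 63 |

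**3. Power with 30 per arm** (two-sample t, two-sided 5%). The article does not say whether the 0.5 is in SDs of the score or of its change, so both readings are shown. On the score reading, the standardised effect is 0.5/√(2(1 − r)) for the change contrast and 0.5/√(1 − r²) for the adjusted one. On the change reading, it is 0.5 for the change contrast and 0.5/√((1 + r)/2) for the adjusted one.

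| Assumed r | Score SD: change → adjusted | Change SD: change → adjusted |
|---|---|---|
| 0.3 | 36% → 52% | 48% → 66% |
| 0.5 | 48% → 59% | 48% → 59% |
| 0.7 | 69% → 76% | 48% → 54% |
| 0.8 | 85% → 89% | 48% → 52% |
| 0.9 | 99% → 99% | 48% → 50% |

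The readings coincide at r = 0.5, where the SD of the change equals that of the score.

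**4. Equal baseline means.** In one simulated three-visit data set of 60 participants, the standard error of the week-12 arm effect was 0.2219 from the group-by-time model and 0.2043 with baseline means constrained equal. The variance ratio is (0.2043/0.2219)² = 0.85. This route gives the same kind of gain as a covariate.

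**5. Age stratum.** In that data set, adding age as a main effect to the group-by-time model left the standard error at 0.2219, because a term constant over time cancels from within-person change. Trials of 60 were also simulated with blocks of four in two age strata, 4,000 runs per setting. Age was assumed to explain 5% or 15% of score variance, and r was 0.5 or 0.7.

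- Change contrast: type I error 4.8% to 5.4%, with or without age.
- Unadjusted week-12 comparison: 3.6% to 4.5%, so conservative.
- Baseline-adjusted model: adding age raised power from 58.9% to 59.3%, 58.4% to 60.7%, 76.2% to 76.4% and 74.1% to 75.2%, which is about 0 to 2 points.

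**The case against.** The strongest reply is that this is efficiency, not error. Baseline is used, the change contrast is unbiased under randomisation, no stated figure is wrong, and the article calls the trial exploratory and admits low power. All of that stands. A reader might infer that the analysis ignores baseline or is invalid; the model text does not support either.

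A second reply is that covariates are often left to a statistical analysis plan that is not shown. For age this has force: the article does not say that age will be excluded, so its absence shows only that the published model does not name it. For baseline it has much less force, because the article itself fixes baseline as a level of time and fixes the contrasts.

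A third reply concerns what a reader might infer about age, namely that omitting the stratum makes the standard errors of the planned analysis too large. The calculations do not support this for the change contrast. It holds only for an unadjusted week-12 comparison. The article mentions t and Mann-Whitney tests for quantitative variables in general, but assigns the continuous primary outcome to the mixed model, so such a comparison is not the stated primary analysis.

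Finally, the size of the gain cannot be read from the documents, since r is not given and the SD behind the 0.5 is not identified. That is right, and the figures are conditional for that reason.

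**Conclusion.** The point holds as one of avoidable imprecision. The published primary model yields a change-score contrast, and adjusting for baseline memory multiplies its variance by (1 + r)/2. The saving is 35% to 5% for assumed r from 0.3 to 0.9, given equal variances at the two visits and complete data. Its direction does not depend on how the 0.5 SD is read, but the power figures do.

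A reader might infer that adjustment rescues the reduced sample. It does not in general. If the 0.5 is in SDs of the change, power reaches only about 50% to 66%. If it is in SDs of the score, adjusted power passes 80% only for r somewhere between 0.7 and 0.8 or higher, where the change contrast is already close to that level.

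The reason to include the age stratum is agreement between analysis and randomisation; little precision should be expected from it.

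**What to change.** State the primary model as composite memory z at weeks 12 and 24, with arm, visit, arm × visit, baseline composite z, baseline × visit and age stratum (45-60 / 61-75), and take the arm difference at week 12 as the primary contrast. A longitudinal model with all three visits, baseline means constrained equal between arms and the age stratum would serve equally well. Use the same covariates for the secondary cognitive z scores. In the same edit, say whether the 0.5 in the sample size section is in SDs of the score or of its change.

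The cost is wording and a few degrees of freedom. Both variables are already collected, and by the article's timeline analysis starts only after data collection ends in June 2026, so the change can be recorded before the analysis starts.

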## Methods

### Study Design

This study will follow a double-blind, randomized, placebo-controlled trial design with 3 phases of assessment: baseline evaluation (week 0), postintervention assessment at 12 weeks, and follow-up assessment at 24 weeks.

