### Follow-Up

There are 3 in-person primary data collection points in the study: “baseline evaluation (week 0),” “postintervention assessment at 12 weeks,” and “second follow-up assessment at 24 weeks.” Between the in-person visits, participants will receive weekly telephonic follow-up calls to promote participant retention, monitor medication adherence, and collect information on any SAEs. In the case of any SAEs, participants will be instructed to discontinue the study medication immediately and to contact the study team for appropriate medical evaluation. In such scenarios, unblinding will be done by the statistician who has access to the randomization and conveyed to the treating medical team. Following completion of the 12-week intervention period, participants will return to the hospital for a comprehensive follow-up visit, which will include assessment of primary and secondary outcome measures; and blood sample collection for postintervention metabolomic analysis, and repeat laboratory investigations, including hematological, hepatic, and renal function tests. Participants will be allowed to withdraw from the study if they wish to do so, and the reason for withdrawal will be clearly documented. They will be encouraged to return the used bottles at the end of 12 weeks or if they withdraw from the study at any time point, for pill count to confirm adherence. The second follow-up assessment will take place at 24 weeks and will include detailed cognitive evaluation. Blood sampling will not be done at this time point. Participants will continue to receive posttrial standard of care from their treating physicians.

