### Strengths and Limitations

The strengths of the study include a double-blind, randomized, placebo-controlled trial design, which is considered the gold standard for evaluating intervention efficacy, clearly defined relevant predictor variables and primary and secondary outcomes; a standardized and culturally validated cognitive battery tailored for the Indian population; and the use of standardized *B. monnieri* (with 50% bacosides) formulation and a matching placebo, ensuring consistency in dosage and bioactive content across participants. The second assessment at 24 weeks (12 wk after the intervention is stopped) will inform about the sustainability of cognitive changes and differences, if any, in the 2 groups. Finally, integration of metabolomics with the clinical outcomes will provide mechanistic insights on the actions of *B. monnieri* on cognition. The limitations include the exploratory nature of the study, lack of sufficient power to evaluate the efficacy, lack of biomarkers to confirm the etiological diagnosis of AD, and a relatively short follow-up period to observe meaningful change in cognitive functions.

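### Last observation carried forward in the intention-to-treat analysis sets early dropouts' memory change to zero and copies end-of-treatment scores into the off-drug week-24 visit; the resulting bias depends on a dropout pattern the protocol does not give

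*Protocol article*

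**What the plan says.** Under Planned Analyses the protocol fixes one rule for missing values: "To handle any missing data, analysis of last observation carried forward will be undertaken within the intention-to-treat analysis model". The only other analysis set named is per protocol, and no other missing-data method is given.

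The same paragraph specifies "Generalized linear mixed models with a between-subject factor of group (treatment vs placebo) and within-subject factor of time (baseline, mid-point, end point"), followed by "Planned simple contrasts will be conducted to assess all time points (baseline vs. 12 wk, 12 wk vs. 24 wk, and baseline vs 24 wk").

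The Study Design section lists three assessments: "baseline evaluation (week 0), postintervention assessment at 12 weeks, and follow-up assessment at 24 weeks". The Follow-Up section agrees: "There are 3 in-person primary data collection points in the study". The weekly calls between visits serve retention, adherence and safety, so they yield no cognitive scores.

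The Outcomes section says: "The primary outcome will be change in the composite *z* score of memory between the 2 groups at 12 weeks". Memory at week 24 is a secondary outcome. Tablets are taken for 12 weeks, and Strengths and Limitations says that the week-24 assessment "will inform about the sustainability of cognitive changes and differences".

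Under Sample Size Estimation: "The sample size was further adjusted for a dropout rate of 20" per cent, giving 38 per arm. Neither the timing of that dropout nor its split between arms is stated.

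**The concern.** Carry-forward assumes that a person's score stays where it was last seen. The visit schedule makes that assumption do two things here.

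- **Lost before week 12.** The only score is the baseline, so the week-12 change is set to exactly zero. Zero is not a neutral value. Participants qualify by scoring at or below the 15th percentile on verbal or visuospatial memory tests, and those two kinds of memory make up the primary composite. Retest gains and regression to the mean are therefore plausible in both arms.
- **Seen at week 12, lost by week 24.** A score taken at the end of treatment stands in for one taken 12 weeks off treatment. The person's week-12 to week-24 contrast becomes zero at the visit that is meant to show whether any change lasts.

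Unequal dropout cannot be ruled out. The Discussion reports, from a study of 46 healthy volunteers at 300 mg for 12 weeks, nausea in 18% on Bacopa against 4% on placebo, and fatigue in 14% against 4%.

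At stake are the effect estimate and its interval. In a trial that describes itself as exploratory and short of power, these are the main product. The mixed model in the same paragraph can use incomplete records without imputation, so the carry-forward step is avoidable.

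**Working it through.** **The plan's own figures.** For 0.5 SD, two-sided 5% and 80% power, the two-sample t-test needs 63.8, so 64 per group. Inflating for 20% dropout gives 64/0.8 = 80 per group. The feasibility size gives 30/0.8 = 37.5, so 38 per group. All agree with the protocol.

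**Inputs.** From the protocol: 38 per arm, 20% dropout, effect 0.50 SD, visits at weeks 0, 12 and 24. Assumed: SD of change 1, dropout at random, placebo mean change *m*, dropout shares dA (active) and dP (placebo) before week 12, and a benchmark in which those who leave would have had the same effect as those who stay.

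**Week 12, expected difference under carry-forward:** (1 − dA)(m + δ) − (1 − dP)m, where δ is the true effect.

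| Case | δ | m | dA | dP | Carry-forward estimate |
|---|---|---|---|---|---|
| All 20% early, equal arms | 0.50 | any | 0.20 | 0.20 | 0.8 × 0.50 = 0.40 |
| Half of it early, equal arms | 0.50 | any | 0.10 | 0.10 | 0.9 × 0.50 = 0.45 |
| No effect, equal arms | 0 | any | 0.20 | 0.20 | 0 |
| Unequal, retest gain | 0.50 | 0.3 | 0.25 | 0.15 | 0.75 × 0.8 − 0.85 × 0.3 = 0.345 |
| Same, no effect | 0 | 0.3 | 0.25 | 0.15 | 0.225 − 0.255 = −0.03 |
| More unequal | 0.50 | 0.3 | 0.30 | 0.10 | 0.56 − 0.27 = 0.29 |
| Reverse split | 0.50 | 0.3 | 0.10 | 0.30 | 0.72 − 0.21 = 0.51 |

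In the first case 0.2 × 76 = 15.2, so about 15 participants (7 or 8 per arm) would have a primary outcome set to zero.

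**Interval and power, first case with m = 0.**
- With a share p = 0.8 observed, the variance of a carried-forward change with mean μ is p(1 + μ²) − (pμ)². This is 0.84 in the active arm (μ = 0.5) and 0.80 in the placebo arm (μ = 0).
- Standard error under carry-forward: √((0.84 + 0.80)/38) = 0.208. In simulation the mean reported standard error and the actual spread of the estimates were both about 0.207.
- Standard error from observed scores (0.8 × 38 = 30.4 per arm): √(2/30.4) = 0.256.
- Estimate over standard error: 0.40/0.208 = 1.92 under carry-forward, against 0.50/0.256 = 1.95 from observed scores. Simulated power is about 46-47% against 48% (m = 0.3 and m = 0).
- The interval is off-centre by 0.10/0.208 = 0.48 standard errors. Coverage of 0.50 is Φ(1.96 + 0.48) − Φ(−1.96 + 0.48), or about 92%; simulation agrees.

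**Week 24.** Let e be the share lost before week 12, l the share lost between weeks 12 and 24, and r the effect truly remaining. Take equal arms, no placebo change and a week-12 effect of 0.50. The carry-forward estimate is (1 − e − l)r + 0.50 l.

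| e | l | r | Estimate | Error |
|---|---|---|---|---|
| 0 | 0.10 | 0 | 0.05 | +0.05 |
| 0 | 0.20 | 0 | 0.10 | +0.10 |
| 0.10 | 0.10 | 0.25 | 0.20 + 0.05 = 0.25 | 0 |
| 0.10 | 0.10 | 0.50 | 0.40 + 0.05 = 0.45 | −0.05 |

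Late dropouts pull the week-24 result towards the week-12 effect. Early dropouts carry baseline forward and pull it towards zero.

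**The case against.** Three stronger readings are tempting, and the documents support none of them.

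1. **That the confidence interval is too narrow.** The carry-forward standard error is about 0.8 of the observed-data one, so a reader might infer false precision. But the two estimators aim at different quantities, and the reported standard error matches the actual spread of the carry-forward estimate. Coverage of 0.50 falls because the interval is mis-centred. With no true effect and equal random dropout, coverage stays at about 95%.
2. **That the week-12 result is always biased.** With no true effect and equal random dropout there is no bias in the mean difference. With equal dropout, a real effect is diluted and no false positive is created. Even the unequal null case (25% against 15%) shifts the difference by only −0.03 SD and leaves the rejection rate near 5%.
3. **That week 24 is always pulled towards a sustained effect.** Early dropouts work the other way, and the net error can be positive, zero or negative.

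Other objections stand in part. The 0.40 figure puts all the dropout before week 12, although the protocol gives no timing, plans weekly retention calls, and does not treat people who stop tablets but attend visits as missing. It also assumes that those who leave would have kept the full benefit. The mixed model is no complete cure: with no visit between weeks 0 and 12, an early dropout supplies no post-baseline score, so the week-12 estimate is close to an observed-case one and rests on missing-at-random. Covariance structure and degrees of freedom are ordinary analysis-plan detail, and their absence here is no fault.

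None of this defends the rule itself. It is stated in the protocol, covers any missing data, and replaces a weaker assumption with a stronger and less plausible one.

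**Conclusion.** The point holds in conditional form. The stated rule sets the primary change of every participant lost before week 12 to zero, and puts end-of-treatment scores into the off-drug visit for those lost later. The direction and size of the bias depend on the timing and arm split of dropout, which the protocol does not give.

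For equal random dropout within the planned 20%, the dilution of a true 0.50 SD effect is at most 0.10 SD (to 0.40), with about 92% coverage and almost no loss of power. Unequal dropout with an assumed 0.3 SD retest gain can move the estimate further: to 0.345 SD at 25% against 15%. At week 24 the error in the cases shown runs from −0.05 to +0.10 SD.

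These figures assume an SD of change of 1 and dropout at random. The damage falls on the estimate, its interval and the durability result far more than on the false-positive rate. In a trial that calls itself exploratory, this is a should-fix.

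**What to change.** Delete last observation carried forward as the intention-to-treat method. State that the intention-to-treat analysis is the mixed model already planned, fitted by likelihood to all observed scores of all randomised participants under missing-at-random. Record the change before unblinding; the protocol starts analysis only after data collection ends in June 2026.

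Add a sensitivity analysis for departures from missing-at-random, for example multiple imputation with a delta shift or a placebo-based assumption, because the model has no post-baseline score for early dropouts. If carry-forward is kept at all, label it a sensitivity analysis.

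The cost is a sentence or two of analysis wording and no new data. The downsides are reliance on missing-at-random and a somewhat wider interval (standard error about 0.256 against 0.208 in the 20% early-dropout case).

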## Abstract

**Background:**

Amnestic mild cognitive impairment (aMCI) represents a transitional stage between normal aging and Alzheimer disease (AD), where early intervention is critical for preserving cognition and delaying or preventing progression to dementia. Due to the limited availability of curative pharmacological treatments, there is growing interest in traditional and indigenous medicinal interventions, such as *Bacopa monnieri* (Linn.) or Brahmi, a widely used Ayurvedic nootropic herb. *Bacopa* consumption is known to enhance cognitive performance in healthy individuals and is associated with alterations in pathways related to branched-chain and aromatic amino acid biosynthesis. These pathways have been implicated in MCI due to AD pathophysiology. Hence, the efficacy of *Bacopa* in aMCI and the mediating metabolic changes need to be systematically evaluated through clinical trials.

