To evaluate the role of *Bacopa* in people with cognitive impairment, Basheer et al [25] did a meta-analysis on the effectiveness of *B. monnieri* in mild, moderate, or severe dementia due to AD or MCI-AD. The authors found no difference between *B. monnieri* and the placebo or donepezil. The analysis included 5 eligible studies; 2 compared *Bacopa* with donepezil, and the rest compared Bacopa with placebo. There was heterogeneity in dosage, duration, formulation, follow-up, and outcomes, and the overall quality of evidence was very low due to high risk of bias, small sample size, and wide CIs. However, no major safety issues were reported in the included trials.

Recently, Minale et al [26] used liquid chromatography-mass spectrometry (LC-MS) in healthy individuals (age range, 55‐80 y) who had consumed *Bacopa* extract for 12 weeks and showed changes in metabolites (aminoacyl-transfer RNA biosynthesis, aromatic and branched-chain amino acid biosynthetic pathways) in plasma, urine, and feces. Prior research findings on blood and cerebrospinal fluid metabolites in AD and MCI have suggested possible alterations in metabolomic pathways associated with cellular energy and biosynthesis, oxidative stress, amino acid utilization, lipid homeostasis, mitochondrial oxidative metabolism, and neurotransmitters [27-31]. Yilmaz et al [32] combined proton nuclear magnetic resonance spectroscopy, plasma LC-MS, and machine learning statistical approaches in a community-based sample cohort acquired from different sites across the United States and reported significant perturbations in amino sugar, alanine, glucose-alanine cycle (energy supply to muscles and nitrogen disposal), cysteine and aspartate metabolism, and urea cycle in patients with MCI compared with healthy controls. Our recent work using untargeted metabolomics in Indian patients with AD (vs cognitively normal controls) showed disruptions in branched-chain amino acid metabolism, nicotinamide metabolism, the tricarboxylic acid cycle, and neurotransmitter pathways [33]. Although the study by Minale et al [26] in healthy subjects suggests that *Bacopa* may affect pathways implicated in MCI and AD, it needs further validation.

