Given the complexity of AD pathophysiology, omics-based investigations of molecular and cellular pathway disruptions are gaining momentum, as they can guide biomarker and therapeutic development. From a mechanistic perspective, *B. monnieri* has been postulated to have antiapoptotic, antioxidant actions, repairs damaged neurons, stimulates kinase activity, restores synaptic function, and improves neurotransmission. A systematic review of 22 studies reported that *B. monnieri* reduces the levels of proinflammatory markers, oxidative stress, and also reduces nuclear factor-κB phosphorylation [52]. However, there is a lack of adequate clinical research on the molecular targets and pathways of *Bacopa* in modulating neuroinflammation and neurotrophism. In our previous work using untargeted metabolomics in Indian patients with AD, we found significant disruption in branched-chain amino acid metabolism, and *Bacopa* consumption for 12 weeks has been shown to alter metabolites of this pathway in healthy adults [33]. We intend to gain better mechanistic insights through the rigorous RCT design of this study and also correlate metabolomic changes with cognitive outcomes.

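### The amino acid pathways given as the metabolic rationale get no prespecified test; a short named family, fixed before unblinding, would be a cheap improvement to an exploratory secondary objective

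*Protocol article*

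**What the plan says.** **Rationale.** The Abstract (Background) says Bacopa use "is associated with alterations in pathways related to branched-chain and aromatic amino acid biosynthesis" and links those pathways to MCI due to AD. The Introduction (Background) says the healthy-adult metabolomic study suggests that Bacopa "may affect pathways implicated in MCI and AD, it needs further validation". It also reports branched-chain disturbance in the group's own AD cohort. The Discussion (Principal Findings) returns to the branched-chain pathway and says the investigators intend to "also correlate metabolomic changes with cognitive outcomes".

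**Objective.** Under Objectives, the one hypothesis stated is about memory at 12 weeks. The metabolomic objective is secondary and open: to find altered metabolites, pathways and networks.

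**Analysis.** Planned Analyses says "Comprehensive statistical and functional analysis pertaining to the metabolomics will be performed using MetaboAnalyst version 6.0". It lists principal component analysis, partial least squares discriminant analysis, ANOVA, heat maps, and pathway analysis with KEGG and the Human Metabolome Database, all on observed peaks. No metabolite or pathway is named for its own test. The only threshold in the section is two-tailed P<.05, and no correction over features is given. Data Processing keeps peaks with a pooled-QC coefficient of variation below 30% but gives no feature count.

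**Size.** Sample Size Estimation: "a sample size of 60 (30 in each group) is determined for this exploratory study based on feasibility", then "adjusted for a dropout rate of 20% and 76 participants (38 in each group) will be recruited".

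**The concern.** The article points to a specific earlier result, says it needs validating, and then analyses the relevant metabolites exactly like all the others. A result can only be validated if it is named before the data are seen. Picked out of a screen afterwards, an amino acid signal is another exploratory observation, however well it fits the story. If the screen is properly corrected, the few metabolites with a prior reason to move share the multiplicity cost of hundreds without one.

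The metabolite-cognition correlation in the Discussion has the same weakness, because it is open to any feature. What is at stake is whether blood samples the trial already takes can say anything firm about the one metabolic finding it cites as motivation.

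**Working it through.** **1. The plan's own figures.** Inputs from Sample Size Estimation: "a clinically relevant effect size as a SD change of 0.5", and "a 2-sided α at 5%, and 80% power, a sample size of 128 (64 in each group) was calculated". These are set for the memory composite. The noncentral t with 64 per arm and 0.5 SD gives 80.1% power, so 128 reproduces. Dropout: 64/0.8 = 80 per arm (160), and 30/0.8 = 37.5, rounded up to 38 per arm (76). Both reproduce.

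**2. Assumptions the document does not supply.** Feature count m = 100 to 1,000; true metabolite shift 0.5, 0.8 or 1.0 SD; 5% Benjamini-Hochberg (BH) as the correction if one is used; six amino acids, correlated 0.5, shifted by the same amount; all other features null and independent.

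**3. Smallest shift detectable with 80% power, 30 per arm** (normal approximation, Bonferroni over m tests): d = (z for two-sided 0.05/m + z for 0.80) × √(2/30).
- 1 test: 0.72 SD
- 6 tests: 0.90 SD
- 100 tests: 1.12 SD
- 1,000 tests: 1.26 SD

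**4. Average power per named amino acid**, simulated with two-sample t tests (1,500 to 2,000 runs, error about one percentage point):

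| True shift | Holm, six tests | BH, m=100 | BH, m=300 | BH, m=1,000 |
|---|---|---|---|---|
| 0.5 SD | 27% | 8% | 3% | 2% |
| 0.8 SD | 74% | 42% | 29% | 18% |
| 1.0 SD | 94% | 74% | 61% | 45% |

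The 8% entry varies between 6% and 8% with the run and the assumed correlation.

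**5. Chance that at least one of the six is confirmed.**
- 0.8 SD: about 94% with Holm, against about 70%, 56% and 40% in screens of 100, 300 and 1,000.
- 1.0 SD: about 99%, against about 93%, 85% and 74%.

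**6. If more features truly change.** With 10% of features changed (independent features), BH power is about 48% to 50% at 0.8 SD and 81% at 1.0 SD.

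**7. If only P<.05 applies.** Power per feature at 30 per arm is 48% at 0.5 SD and 86% at 0.8 SD, so power is no longer the main problem. Expected chance findings are 0.05 × m: 5 at m = 100 and 50 at m = 1,000. If none of the six amino acids moved and they were independent, at least one would still pass with probability 1 − 0.95^6 = 26%.

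**Limits.** These are feature-wise tests. Pathway enrichment is not modelled, nor is the precision gained from baseline adjustment.

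**The case against.** **No metabolic hypothesis is stated.** A reader might infer from the Abstract and Introduction that the trial sets out to confirm an amino acid hypothesis and has failed to test it. The document does not support that. Its formal hypothesis is memory only, the metabolomic objective is discovery, the method is declared untargeted, and the study is called exploratory. The remark about validation describes an earlier study and is not a commitment to a confirmatory test. This part of the objection stands in full.

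**The screen would not always fail.** A reader might also infer that an all-feature screen would usually miss the amino acids. That depends on a correction, a feature count and an effect size the document does not give. It is untrue for at least one hit at 0.8 SD with 300 features or fewer, untrue at 1.0 SD, and untrue at uncorrected P<.05 with 0.8 SD.

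**Pathway analysis is planned.** The rationale is worded at pathway level, and KEGG scoring works at that level. True, but the named pathways would be entries in a full list with no prior standing.

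**A separate analysis plan may name the targets.** Possible, and such detail is often left there. If it does, a cross-reference closes the point. What can be judged here is the analysis the article chose to describe.

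**The list is a judgement.** The Introduction also mentions other pathways, and the Discussion returns only to branched-chain metabolism. Hence the list should be the sponsor's.

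**Conclusion.** The point holds as a cheap improvement to an exploratory secondary objective. The article gives branched-chain and aromatic amino acid pathways as its reason for looking, but describes no analysis that treats them differently from any other peak. Under a 5% BH screen, the cost at 0.8 SD is a fall in average power from about 74% to between 42% and 18%. At 0.5 SD it is a fall from about 27% to between 8% and 2%. Without a correction the cost is credibility, since 5 to 50 chance findings would surround any amino acid hit.

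The direction holds in every corrected scenario tabulated; the size rests on the assumed feature count, shift and correction. It does not follow that the named family would settle the question: at 0.5 SD, the only effect size in the document and one set for memory, it averages only 27% power. Nor is the planned untargeted analysis wrong for the objective as written.

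**What to change.** Before unblinding, add one paragraph to Planned Analyses:

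- Name one short family drawn from the stated rationale. Leucine, isoleucine, valine, phenylalanine, tyrosine and tryptophan are an example; the sponsor sets the final list.
- Test each by the Bacopa-placebo contrast in week-12 log level, adjusted for that metabolite's own baseline level, with Holm at 5% across the family.
- If a metabolite is measured in more than one of the four column and polarity modes, keep the mode with the lowest pooled-QC coefficient of variation.
- Use the same family, with arm in the model, for the metabolite-memory correlation in the Discussion.
- Report all other features and pathways separately as discovery.

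If an analysis plan already fixes such a list, cite it instead.

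**Cost:** a paragraph of wording, with no new assay, sample or visit. By the stated timeline, data collection ends in June 2026 and analysis follows, so there is time. The downside is that the sponsor commits to the list before seeing the data. The report should also say that a null result in this family, at about 30 per arm, does not rule out a moderate effect.
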